## 2.5 Secondary outcome measures

- Post-operative complications
- Post-operative morbidity
- Quality of recovery
- Cardiac and renal impairment
- Overall survival (OS) at 3- and 5-years

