### 2.5.1 Definition of secondary outcome measures

Post-operative complications: Assessed with Clavien-Dindo classification up to 30 days postoperatively (44).

Post-operative morbidity: Will be assessed by the postoperative morbidity score (POMS) on postoperative day 3 and 5 (45).

Quality of recovery (QoR): Will be assessed the day before surgery and 3 days after surgery with the QoR-15 questionnaire (46, 47).

Overall survival: Survival time is calculated from the date of randomization to the date of death (all-cause), or for patients still alive to the date of last clinical follow-up or contact.

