| Blood-samples                                                                      | X                      |                | X                    | X                    | X                    |                       |                                          |                                         |                               |                      |                       |                       |
| Quality of recovery Swe-15 Questionnaire                                           | X                      |                |                      | X                    |                      |                       |                                          |                                         |                               |                      |                       |                       |
| Randomisation                                                                                  |                        | X              |                      |                      |                      |                       |                                          |                                         |                               |                      |                       |                       |
| Record operative report                                                                        |                        | X              |                      |                      |                      |                       |                                          |                                         |                               |                      |                       |                       |
| Treatment according to randomisation                                                           |                        | X              | X                    | X                    |                      |                       |                                          |                                         |                               |                      |                       |                       |

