 Hb (g/L) CRP (mg/L), Troponin T (ng/L), Albumin (g/L), Natrium (mmol/L), Kalium (mmol/L), eGFR1 (ml/min/1,73m^2), Creatinine (micromol/L), S-Transtyretin, P-Fibrinogen, S-Prokalcitonin, CA-125 (kE/L), CEA (microg/L, only preop). see Appendix 17.4. see Appendix 17.2. Collected at beginning and end of surgery. 40 mL of blood. Before infusion of chemotherapy.

*The IPLA –OVCA trial protocol version 3.2.1, 2021-01-28*

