### 8.3 Data analyses

The primary endpoint, time to start of adjuvant chemotherapy will be analyzed using a linear regression model including the variable treatment. Results will be presented as the mean difference in days together with 95% confidence intervals and a Wald-test p-value. The significance level in the main analysis is set to 5%. Regression models including different clinical factors will also be estimated to take potential confounding into account. All analyses of primary and secondary outcome will be performed according to the intention-to-treat principle but may also be presented as per-protocol. For safety data, patients will be analyzed according to per-protocol approach.

Differences in complications, morbidity and in cardiac and renal impairment will be tested using Chi-square tests of independence. For dichotomous outcomes result will also be presented as differences in proportions together with 95% confidence intervals. Overall survival time will be calculated from the date of randomization to the date of death. For patients still alive, survival time will be calculated from the date of randomization to the date of last visit. Results from the survival analysis will be graphically presented as Kaplan-Meier curves. Proportional hazards regression models will be used to estimate the effect of the intervention on time to death. Results will be presented as hazard ratios 95% confidence intervals and Wald test p-values.

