### 16.2 Post-operative morbidity score (POMS)

Post-operative morbidity according to the post-operative morbidity score (45)

| Morbidity type | Criteria                                                                                                                 | Source of data      |
|----------------|--------------------------------------------------------------------------------------------------------------------------|---------------------|
| Pulmonary      | Has the patient developed a new requirement for oxygen or respiratory support?                                           | Patient observation |
|                |                                                                                                                          | Treatment chart     |
| Infectious     | Currently on antibiotics and/or has had a temperature of >38°C in the last 24 hr.                                        | Treatment chart     |
|                |                                                                                                                          | Observation chart   |
| Renal          | Presence of oliguria <500 mL/24 hr; increased serum creatinine (>30% from preoperative level); urinary catheter in situ. | Fluid balance chart |
|                |                                                                                                                          | Biochemistry result |
|                |                                                                                                                          | Patient observation |

| Morbidity type   | Criteria                                                                                                                                                                                                                                                                                                       | Source of data      |
|------------------|----------------------------------------------------------------------------------------------------------------------------------------------------------------------------------------------------------------------------------------------------------------------------------------------------------------|---------------------|

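### The chi-square test is the only test named for cardiac and renal impairment, an undefined outcome, although troponin T, creatinine and eGFR are measured serially; a baseline-adjusted marker analysis should be added

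*Protocol*

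**What the plan says.** "Cardiac and renal impairment" is one of the five secondary outcomes in Protocol section 2.5, and it appears again in the synopsis and in section 8.2. Section 2.5.1 defines the other four (complications, morbidity, quality of recovery, overall survival) and is silent on this one.

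Section 8.3 nevertheless fixes the test: "Differences in complications, morbidity and in cardiac and renal impairment will be tested using Chi-square tests of independence". It adds: "For dichotomous outcomes result will also be presented as differences in proportions together with 95% confidence intervals". No other analysis of this outcome is named.

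The schedule of events (section 3.2) has a "Blood-samples" row marked at baseline and on postoperative days 1, 3 and 5. Its footnote lists "Troponin T (ng/L"), eGFR and creatinine among the assays.

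The one numerical renal criterion is in the renal item of the morbidity score (appendix 16.2): "increased serum creatinine (>30% from preoperative level"). There it is one alternative beside oliguria and a urinary catheter in place. That score belongs to a different outcome: "Post-operative morbidity: Will be assessed by the postoperative morbidity score (POMS) on postoperative day 3 and 5". Its cardiovascular item contains no troponin threshold.

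**The concern.** A chi-square test needs categories. If the outcome comes from the scheduled markers, the plan turns repeated continuous measurements, each with a preoperative value, into a yes/no result, and the named test has no baseline term. That discards information, and more of it the less common impairment is.

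The result bears on harm as well as benefit. The risk section (9.1) names hypotension and arrhythmias as signs of local anesthetic toxicity, and the intraperitoneal ropivacaine is given in addition to epidural ropivacaine (section 5.3). A non-significant chi-square test could be taken as reassurance about heart and kidney when only very large differences would have been detectable.

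**Working it through.** **1. Evaluable number.** Section 8.4 gives a difference of 5 days, SD 12, two-sided 5% and 80% power. Per arm: 2 × (1.960 + 0.842)² × 12² / 5² = 90.4, rounded up to 91, so 182 in total. This matches the protocol. The document gives no power figure for cardiac or renal impairment.

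**2. Assumptions.** The protocol gives neither the share of women who will be called impaired (p) nor the correlation between preoperative and postoperative marker values (r). I take p = 10%, 20%, 30% and r = 0.5 to 0.7, with an approximately normal (log) marker and a small uniform shift between arms.

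**3. Binary cut against the unadjusted continuous marker.** Relative efficiency = φ(c)² / [p(1 − p)], where c is the normal quantile that leaves p above it.

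- p = 10%: 0.1755² / 0.09 = 0.34
- p = 20%: 0.2800² / 0.16 = 0.49
- p = 30%: 0.3477² / 0.21 = 0.58

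A cut at the median would keep 0.64.

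**4. Binary cut against a baseline-adjusted regression.**

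If the cut ignores baseline, multiply step 3 by (1 − r²). If the cut is on change from baseline, multiply by (1 − r²) / [2(1 − r)] = (1 + r)/2.

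| p | Cut ignores baseline, r = 0.5 | Cut ignores baseline, r = 0.7 | Cut on change, r = 0.5 | Cut on change, r = 0.7 |
|---|---|---|---|---|
| 10% | 0.26 | 0.17 | 0.26 | 0.29 |
| 20% | 0.37 | 0.25 | 0.37 | 0.42 |
| 30% | 0.43 | 0.29 | 0.43 | 0.49 |

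The ranges are therefore about 17–43% for a cut that ignores baseline and about 26–49% for a cut on change.

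**5. What the chi-square test can detect.** Assume 20% impaired on placebo and 91 per arm (normal approximation, pooled variance under the null). For a fall to 6%: mean proportion 0.13; null standard error √(0.13 × 0.87 × 2/91) = 0.0499; alternative standard error √[(0.16 + 0.0564)/91] = 0.0488; (0.14 − 1.96 × 0.0499)/0.0488 = 0.87, so power is 81%. The 80% point is therefore at about 6%. In the direction of harm it is a rise to about 39%. With all 110 per arm contributing, the same formula gives a fall to about 7% or a rise to 37%.

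**6. The same comparison as power.** Take the shift for which unadjusted means have 80% power at 91 per arm: 2.802 × √(2/91) = 0.415 SD. With 10%, 20% or 30% of controls impaired, a cut on the postoperative value gives the chi-square test about 30%, 43% or 52% power. Baseline-adjusted regression has about 90% (r = 0.5) to 97.5% (r = 0.7).

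**The case against.** The strongest objection is that nothing ties this outcome to the markers. A chi-square test is the ordinary choice for clinical events, and the abbreviation list contains acute renal failure as well as troponin T, so both an event reading and a marker reading are open. The proportion of women impaired is a legitimate clinical endpoint. The exact marker, day and cut-off may stand in a statistical analysis plan that is not shown. All of this stands: the missing threshold alone is not the point, and the proportion should be kept.

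A reader might infer that the plan applies an absolute cut-off, ignores each woman's baseline and so lets pre-existing disease drive the result. The document does not support that. No absolute cut-off appears, a chi-square test works equally well on an outcome defined as change, and the only numerical renal rule in the document is itself relative to the preoperative value. Under randomisation, pre-existing disease would in any case add noise, not bias.

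A reader might also infer that most of the information is necessarily lost. That depends on p and r, which are assumed. A median cut compared with the unadjusted marker loses 36%. The formulas also assume a uniform shift; if treatment affected only a few women with marked injury, the continuous analysis need not be the better one.

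Finally, drop-out for the primary endpoint need not apply to blood samples on days 1 to 5. Using 110 per arm changes the detectable difference only slightly (step 5).

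**Conclusion.** The point holds in a limited form. The protocol commits to a categorical test as the only test of an outcome it does not define, while scheduling serial continuous markers with a preoperative value. If impairment is derived from those markers, more than half of the information available to a baseline-adjusted analysis is lost throughout the range examined (10–30% impaired, correlation 0.5–0.7). This is so even if impairment is defined as change from baseline. With an assumed 20% impaired on placebo, only a fall to about 6% or a rise to about 39% is detectable with 80% power at 91 per arm. A null chi-square result should therefore not be read as evidence of no cardiac or renal effect. The sizes rest on the assumed share, correlation and normal shift. This is a minor improvement to a secondary endpoint; the primary endpoint and the sample size are unaffected.

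**What to change.** In section 8.3, keep the chi-square test and the difference in proportions. Beside them add a linear regression of log peak troponin T, and one of log peak creatinine, over postoperative days 1, 3 and 5 on treatment, adjusted for the log preoperative value. Report each as a ratio between arms with its 95% confidence interval, and base statements about possible harm on that interval, not on a non-significant test.

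In section 2.5.1, state that the binary outcome is judged against the woman's own preoperative value. For creatinine, the rise of more than 30% already given in appendix 16.2 can be used, without the urinary-catheter item. For troponin T, fix the threshold before unblinding.

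The cost is wording in two sections and one extra analysis per marker; no added samples, visits or patients are needed. The downside is that a ratio of peak values is less direct to read than a proportion, which is why the proportion stays.

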### 8.4 Power and sample size

If the mean time to start of chemotherapy with standard treatment is 31 days (SD=12) the study needs to recruit totally 182 patients in order to detect a reduction in time to chemotherapy with 5 days (from 31 to 26 days) in the experimental group, using a two-sided significance level of 5% and a power of 80%. To compensate for a possible 20% drop out rate the target sample size is set to 220 patients.

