### 4.4 Randomization and registration

After verification of eligibility and signed informed written consent, women will be randomised at the morning of surgery to receive either Ropivacaine or saline by equal allocation, 1:1. The randomisation procedure will be pre-stratified for participating centre (permuted block design).

The Clinical Trials Unit at Centre for Clinical Cancer Studies Theme Cancer, Karolinska University Hospital, Stockholm, Sweden will perform the randomization centrally. All inclusion criteria and no exclusion criteria must be met. Inclusion and exclusion criteria are entered into the randomization/registration application, which is a web-based instrument (ALEA). Username and password are required to log in; each investigator authorized to register patients has a personal login user name and password. If all criteria are met, patients are registered, and the allocated patient study number is recorded in the patients' medical file. After randomization, confirmation e-mail will be sent out to the investigator, research nurse and principal investigator. Randomization will be performed by unblinded dedicated nurses not involved in the study in any other aspect. Each participating center

allocates one dedicated nurse (and one back-up nurse) who will be authorized to enter the web-based randomization system. After randomization a unique study number will be generated for each participant. The code list will be retained in a locked area only accessible to the unblinded nurse (-s).

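### Minor arithmetic error in Protocol 8.4: 220 patients do not offset the stated 20% drop-out, since 20% loss leaves 176 evaluable against the 182 required

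*Protocol*

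**What the plan says.** Section 8.4 of the Protocol assumes a mean of 31 days to chemotherapy under standard treatment, an SD of 12 days, a two-sided 5% significance level and 80% power. On that basis, "the study needs to recruit totally 182 patients in order to detect a reduction in time to chemotherapy with 5 days", from 31 to 26. The next sentence adds the allowance for loss: "To compensate for a possible 20% drop out rate the target sample size is set to 220 patients". The Synopsis repeats 220 as the planned sample size.

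Two other sections fix the form of the calculation. Section 4.4 randomises women "to receive either Ropivacaine or saline by equal allocation, 1:1". Section 8.3 says that the primary endpoint "will be analyzed using a linear regression model including the variable treatment", which is a comparison of two means. The Protocol gives no other drop-out rate and no other basis for 220.

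**The concern.** To keep a required number of evaluable patients after a fraction *d* is lost, the requirement has to be divided by (1 − *d*). Multiplying it by (1 + *d*) gives too few, because the loss is taken from the larger, inflated number. The step from 182 to 220 is a factor of 1.21, while a 20% loss calls for a factor of 1.25.

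What is at stake is the truth of the statement linking 220 patients, 20% drop-out and 80% power. The allowance does real work in this design. Women are randomised on the morning of surgery (4.4), and those whose abdomen is closed without any tumour resection are then excluded from the trial (4.3 and section 6). A woman who never starts adjuvant chemotherapy has no value for the primary outcome as section 2.4.1 defines it. The Protocol gives no rates for either loss.

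**Working it through.** **Inputs.** From Protocol 8.4: difference δ = 5 days, SD σ = 12 days, two-sided α = 5% (z = 1.960), power 80% (z = 0.842), required total 182, drop-out 20%, target 220. From 4.4: 1:1 allocation. From 8.3: comparison of two means.

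**1. The Protocol's 182.** By the normal approximation,

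n per arm = 2 × (1.960 + 0.842)² × (σ/δ)² = 2 × 7.85 × (12/5)² = 90.4, rounded up to 91.

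Total = 2 × 91 = 182. This matches exactly, so 182 contains no allowance for loss and the inputs are not in dispute.

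**2. What 220 leaves after 20% loss.** 220 × 0.80 = 176, or 88 per arm. Shortfall: 182 − 176 = 6.

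**3. What 20% loss would require.** 182/0.80 = 227.5, rounded up to 228. The target is 8 short of that.

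**4. Where 220 may come from.** 182 × 1.2 = 218.4, which rounds up to 219 and is close to 220. This is an inference.

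**5. Power with 176 evaluable.** Standard error of the difference = 12 × √(2/88) = 1.809 days. Power = Φ(5/1.809 − 1.960) = Φ(0.804) = 78.9%.

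**6. Detectable difference at 80% power with 176.** (1.960 + 0.842) × 1.809 = 5.07 days.

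**7. Loss that 220 does cover.** (220 − 182)/220 = 38/220 = 17.3%.

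The same formula at several loss rates:

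| Randomised | Loss | Evaluable | Power |
|---|---|---|---|
| 220 | 0% | 220 | 87.1% |
| 220 | 10% | 198 | 83.4% |
| 220 | 17.3% | 182 | 80.3% |
| 220 | 20% | 176 | 78.9% |
| 228 | 20% | 182 | 80.3% |

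**The case against.** The strongest reply is that the error is too small to matter. It amounts to 6 evaluable patients and about one percentage point of power. The SD is given only as a whole number, and an SD of √(88 × 25/15.70) = 11.84 days would restore 80% power at 88 per arm. The deficit is therefore smaller than the rounding of the Protocol's own input. Section 8.4 also calls the 20% loss possible, not expected, and up to 17.3% loss the target is met. All of this stands, and it makes the point minor. It does not make the sentence true: however 220 was chosen, 80% of 220 is 176.

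Two other defences fail. One is that 182, described as a number to recruit, might already include an allowance; but it is exactly the unadjusted result, and the next sentence adds the allowance on top. The other is that 220 is a rounded figure; but 227.5 does not round to 220, and a number meant to protect against loss is rounded up.

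A reader might also infer that 182 is itself too low, because a calculation with the t distribution gives 184. The Protocol does not support that as an error. Section 8.3 specifies a Wald test without naming a t reference distribution, and a Wald test referred to the normal distribution gives exactly 182.

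**Conclusion.** The statement in 8.4 is wrong as written, by a small amount. At the stated 20% drop-out, 220 patients leave 176 evaluable and power of about 79%, where the text implies at least 182 and 80%. The result rests on the Protocol's own mean difference and SD, on 1:1 allocation with equal loss in the two arms, and on the normal approximation that reproduces 182.

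Two stronger readings go beyond the document. One is that the trial is materially underpowered: the loss is about one point, and it arises only if drop-out exceeds 17.3%, which nothing in the Protocol shows will happen. The other is that the authors multiplied by 1.2: the figures are consistent with that, but the step is not shown, and the finding does not depend on it.

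**What to change.** Keep 220 and replace the last sentence of section 8.4 with wording such as:

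> 220 patients retain the required 182 (80% power) with up to about 17% drop-out; with 20% drop-out (176 evaluable) power is about 79%.

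Both power figures in this wording come from the normal approximation behind 182, so the sentence does not mix methods. The cost is one sentence and a slightly less favourable statement. No patients are added, no analysis changes, and the Synopsis figure stays as it is.

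If the sponsor prefers to keep the 20% allowance with 80% power, the target becomes 228. That is 8 more patients and a change to both 8.4 and the Synopsis. For a gap of about one point of power, restating the sentence is the proportionate choice.

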## 9 Ethical considerations

### 9.1 Risk-Benefit considerations

This study will use an additional drug, ropivacaine, administered intraperitoneally during and after surgery in one group of patients. The drug has been used for > 20 years and is a safe, cheap, long-acting local anesthetic that has analgesic and anti-inflammatory characteristics that can be used for the benefit of patients. It is used for local infiltration, as a spinal anesthetic as well as during nerve blocks. Due to the safety profile of ropivacaine, it has almost completely replaced bupivacaine for routine use, except during spinal anesthesia. There is a risk when using ropivacaine in high doses when local anesthetic toxicity may occur. Symptoms of toxicity include numbness around the mouth, metallic taste on the tongue, light-headedness and later epileptiform seizures. Even hypotension and arrhythmias may occur if cardiovascular manifestations occur due to toxicity. Luckily, these are rare if the drug is administered correctly and in the prescribed maximum doses. However, if the drug is used in doses < 750 mg/day (as recommended by the manufacturers), the risk of systemic toxicity is negligible. In a previous study in 40 patients measuring plasma concentration of ropivacaine following intraperitoneal injection (Fig 3), we found that free plasma concentration of Ropivacaine (that determines toxicity) were much lower than known toxic concentrations in humans and no patient revealed signs or symptoms of systemic LA toxicity (43). In the present study, we plan to use similar doses as we used in this previous study.

[figure not shown]

*Fig 3. Postoperative serum levels of total and free plasma concentration of Ropivacaine in the two groups at 6, 24 and 48 hours after incision.*

There is a potential risk of interaction with opioids and other local anesthetics that may potentiate the effect of ropivacaine. The department is well organized in the potential management of any toxic symptoms and intralipid is easily available and effective.

There is a theoretical risk of catheter-related abdominal infection, however, in our small pilot study we had no catheter related infection. Since the abdominal catheter is inserted under sterile conditions during surgery and a bacterial filter is always used when injecting LA, we do not anticipate any additional risks for participants. However, the patients will be followed-up closely to detect any evidence of infectious complications and start antibiotic management early, if a catheter-related infection is suspected.

In summary, and if our hypothesis is proven correct, it is very much to the advantage for women with advanced EOC subjected to surgery to administer LA, since it may lead to earlier recovery and start of adjuvant chemotherapy. The administration of LA is easy and Ropivacaine is a cheap drug with low toxicity and very few known side effects. The benefits of LA intraperitoneally, if proved, far outweigh the small risk (if any) of systemic toxicity.

